## Abstract

**Background:**

Low back pain and lower extremity sensory and functional abnormalities are common symptoms of lumbar disc herniation (LDH), which can easily cause walking dysfunction and significantly impair the quality of life of patients. Tuina and traditional Chinese exercises (TCEs) are effective in relieving pain and restoring dysfunction, and both are often used in China as a combination of passive therapy and active exercise to ease symptoms in patients with LDH. However, the majority of current clinical trials on the treatment of LDH with Tuina or TCEs are single-centre clinical studies, and the quality of these studies is generally low. Furthermore, clear evidence of clinical efficacy as to whether Tuina combined with TCEs is superior to single TCEs for improving dysfunction and pain in patients with LDH is lacking.

**Methods/design:**

The design is a multicentre, assessor-blinded clinical randomised controlled trial. A total of 166 patients with LDH (aged 18–65 years) were recruited from four centres and randomly assigned at a 1:1 ratio to two groups: the TCE group and the Tuina combined with the TCE group. Each group received three treatments over the course of 1 week for a total of 4 weeks. The primary outcome indicator was the Oswestry Disability Index, whereas the secondary outcome indicators were the Short Form of Quality of Life Scale, the Short-Form McGill Pain Questionnaire Scale, and gait analysis. Assessments were made before the treatment, at the end of the treatment, and at the third and sixth months’ follow-ups. Gait analysis was only used for comparison between the two groups before and after treatment, and did not involve follow-up. Adverse events occurring during the trial were faithfully recorded.

**Conclusion:**

The results of this study are expected to provide a more effective research protocol for symptomatic LDH and an evidence-based rationale for the efficacy and safety of Tuina combined with TCEs in the treatment of symptomatic LDH.

**Clinical trial registration:**

https://www.chictr.org.cn/showproj.html?proj=209956, identifier ChiCTR2300077361.

## Introduction

Lumbar disc herniation (LDH) is a prevalent degenerative condition of the spine, manifesting clinically as low back pain (LBP) and leg pain (1). Epidemiological studies have demonstrated that LBP is one of the 10 leading causes of disability in over 100 countries (2). LDH mostly occurs in middle-aged and young people; with the change of social lifestyle, the incidence of LDH is gradually rising, and a trend of rejuvenation is observed (3). LDH is associated with severe disability, often affecting people’s normal work and life and increasing the economic burden on individuals and society (4).

Currently, the treatments for LDH are categorised into surgical and nonsurgical. Considering effectiveness and safety, nonsurgical treatments have become the first choice for most patients, and about 90% of the patients can obtain significant improvements (5, 6). Nonsurgical treatments for LDH are varied and include medications, acupuncture, traction, physical therapy, and functional exercises; nonsteroidal anti-inflammatory drugs (NSAIDs) are often used as the first line of treatment for LDH (7). NSAIDs are effective in relieving pain but do not improve other symptoms that alleviate LDH; NSAIDS also cause gastrointestinal adverse effects (8, 9). In the pursuit of reducing treatment costs and enhancing therapeutic efficacy, nonpharmacological and complementary therapies such as acupuncture, Tuina and exercise have garnered significant attention (3).

Tuina therapy, a traditional Chinese message therapy, is recommended as a treatment modality for LDH in the guideline due to its significant clinical efficacy, low incidence of serious adverse effects, and low cost (3, 10). A preliminary study on the effect of Tuina on lumbar spine function in patients with LDH found that patients’ visual analogical scale (VAS) scores decreased, lumbar curve index and intervertebral space height increased, and lumbar sagittal Cobb angle increased after undergoing manipulation intervention for 2 weeks, showing significant clinical efficacy (11). Tuina can improve muscle tension, eliminate edema, promote blood circulation, relieve aseptic inflammation, relax muscles and relieve pain by rubbing, pinching and pressing on local tissues (12, 13). Although Tuina can relieve pain, it does not significantly improve the strength of the lower back muscles (13). Therefore, massage therapy can be used in conjunction with exercise therapy, in addition to being used alone. Some studies have demonstrated that the combination of exercise therapy and massage therapy has a positive clinical effect on the management of LBP and the restoration of function (14, 15). In China, Tuina therapy in conjunction with traditional Chinese exercises (TCEs) is often recommended to improve pain and dysfunction in patients with LDH (16).

TCEs are effective nonsurgical treatments for improving the physical and mental health of patients with chronic diseases and can provide significant relief for LBP (17). TCEs enhance spinal stability and chest and lumbar muscle strength to relieve lumbar pain, improve dysfunction, and regulate the patient’s physical and mental health (18–20). In contrast to exercise therapy, TCEs necessitate conscious inhalation and exhalation, as well as the relaxation of mental will, in addition to the appropriate physical exercise, to prevent and treat diseases (21). A systematic review revealed that breathing and meditation, emphasised by TCEs, may be one of the neurophysiological mechanisms of LBP relief in TCEs, in addition to the regulation of strength and flexibility training and pain-related brain networks in TCEs (22). Various types of TCEs include Taiji, Baduanjin, Wuqinxi, and Yijinjing (23). However, TCEs are complex and variable in their movements, and lack a collection of movements that are easily learned and suitable for exercise in individuals with LDH. To identify suitable exercises for LDH patients, an expert questionnaire survey was conducted through the Delphi method. This process involved the screening of four movements from Taiji, Baduanjin, and Wuqiuquan.

At present, clinical trials investigating the nonsurgical treatment of LDH are typically characterised by a limited number of participants and a low level of methodological rigour (24). No clear current evidence of clinical efficacy suggests that treatment with Tuina in combination with TCEs is more effective than TCEs alone in improving pain and dysfunction in patients with LDH. Consequently, the present study proposes to conduct a broader validation study (multicentre, randomised, controlled and assessment-blinded clinical trial) by combining Tuina with TCEs. This approach will be achieved using clinical assessment and gait analysis to validate that combined therapy plays a superior role in improving dysfunction, pain and gait in patients with LDH.

## Methods

### Study design

This study is a multicentre randomised controlled clinical trial study conducted in four clinical centres (Figure 1). The Wuxi Hospital of Traditional Chinese Medicine is the main centre. The Yueyang Hospital of Integrative Medicine affiliated with the Shanghai University of Traditional Chinese Medicine, Wuxi Rehabilitation Hospital and the Wuxi Xinwu District Hospital of Traditional Chinese Medicine are the three subcentres. Patients were recruited through advertisements at each centre. Patients who met the inclusion criteria were randomly assigned to either the TCE group or the Tuina combined with TCE group at a 1:1 ratio. The trial consisted of a four-week intervention period and subsequent three- and six-month follow-up periods. Data were collected before treatment, after 4 weeks of treatment, and at 3 months and 6 months of follow-up. The outcome assessment indicators included the Oswestry Disability Index (ODI), Short Form of Quality of Life (SF-36) Scale, Short-Form McGill Pain Questionnaire (SF-MPQ) Scale and gait analysis, which was used only for efficacy evaluations before and after 4 weeks of treatment.

**Figure 1 fig1:**
[figure not shown]
Flow chart of the pilot study.

### Ethics approval

The study was approved by the Ethics Committee of the Wuxi Hospital of Traditional Chinese Medicine (STHZG2023021301), and it was registered in the China Registered Clinical Trial Registration Centre (ChiCTR2300077361). The study strictly followed the criteria outlined in the Declaration of Helsinki, the Consolidated Standards of Reporting Trials (COMSORT) and the Standardised Program Item: Recommendations for Interventional Trials (SPIRIT) guidelines (25).

### Recruitment

Subjects were recruited at each subcentre through a variety of channels, including printed advertisements, flyer distribution, telephone inquiries, and public announcements on the hospital’s WeChat public website. Each subject participating in the trial must meet the inclusion criteria. Subjects who meet any of the exclusion criteria subject will be excluded. The principal investigator will not request that the subject sign an informed consent form until the subject has had sufficient opportunity to understand the nature of the trial and to agree to participate in it.

### Inclusion and exclusion of subjects

#### Inclusion criteria

Age ≥18 and ≤65 years old, regardless of sex.Meeting the diagnostic criteria for LDH (26).Duration of the disease ≥3 months.VAS scores >3 and ≤7.Voluntarily participation and signed informed consent form.

#### Exclusion criteria

Patients with a history of previous severe spinal trauma.Patients with spinal bone tumours, tuberculosis and osteoporosis, as seen on imaging.Patients with severe neurological deficits, such as cauda equina injury.Patients with a combination of cardiovascular, cerebrovascular, hematopoietic, gastrointestinal and other serious illnesses or psychiatric disorders.Patients with other autoimmune diseases, metabolic disorders, and acute and chronic infections.Patients who have participated in other clinical trials.

Those with one of the above conditions cannot be included in this trial.

### Randomisation, allocation concealment and blinding

The random sequence was generated by a statistician independent of the study through a central randomisation system. The random numbers and group assignments were provided to the independent researcher through the central randomisation system. This researcher was not involved in any other aspect of the trial. The physician only obtained the grouping information from this independent researcher by telephone before the treatment. The central randomisation system had strict limitations on the permissions granted, and only the supervisory staff had access to these documents. This procedure ensured adequate concealment of the randomisation. The study was not blinded to the patients and therapists, but it was blinded to the evaluators. This evaluator was independent of this study. The TCEs therapists were separated from the Tuina therapists, and neither group was aware of the grouping of the patients. Patients were not allowed to interact with the therapist beyond general counseling about their health status at each session.

### Sample size calculation

The trial was designed as a superiority trial with ODI as the primary observation index. The previous study demonstrated that the mean and standard deviation of ODI after 4 weeks of intervention in the TCEs group were 19.73 and 1.94, respectively, whereas the mean and standard deviation of ODI after 4 weeks of intervention in the Tuina combined with TCE group were 14.53 and 2.60, respectively. The sample size was calculated using the following formula:

$$n=\frac{2{\left(Z_{\alpha /2}+Z_{\beta }\right)}^{2}\times \sigma^{2}}{\left(\mu_{t}-\mu_{c}-\Delta \right)}$$

$$\mu_{t}=14.53,\mu_{c}=19.73,\alpha =0.05,\beta =0.2,\sigma =2.60,\Delta =-4$$

The sample size for each group was 74. Because this trial was a superiority trial, the sample size of each group was the same, and the clinical trial was set up in two groups (Tuina with TCE group and TCE group), combined with the relevant regulations. To evaluate the efficacy and safety of this study fully, the total number of cases was planned to be 166 cases, considering the potential for adverse effects. The Wuxi Hospital of Traditional Chinese Medicine was responsible for this project and was the main centre where the case study was undertaken. In other subcentres, the number of cases can be adjusted according to the situation, but no fewer than 30 cases should be in each group in each centre. If enrolment cannot be completed in any centre due to insufficient suitable subjects, the cases were distributed among the centres.

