### Statistical analysis

The data will be subjected to analysis by our team of professional statisticians, who will employ IBM SPSS Statistics V.27.0 for this purpose. To assess the normality of the data, the Kolmogorov–Smirnov test was used. The quantitative results were expressed in terms of the mean and standard deviation. The purpose of the primary and secondary outcome indicators was to assess the difference in efficacy between the two groups. Hypothesis testing was employed to this end. The chi-square test was used to ascertain the dissimilarities in baseline data between the two groups. The analysis of variance for repeated measures was utilised to examine the alterations in efficacy between the two groups before, during and after the intervention, as well as after the follow-up period. For confounding factors that were challenging to regulate or were not regulated prior to treatment, such as an imbalance between the groups prior to treatment, were treated as covariates, and logistic regression was employed to ascertain the variability of efficacy between groups and to eliminate the influence of these factors on efficacy. The data collection and data summarisation were meticulously examined to minimise data anomalies. In the event of missing data, the data were assumed to be missing at random, and multiple interpolation would be employed for analysis. Subjects who were excluded from the trial will be excluded from the data set. The level of statistical significance was set at 5% (*p* < 0.05), and 95% confidence intervals were employed as effect estimates.

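### The sample size is for superiority by a 4-point ODI margin, but the planned analysis tests only for a non-zero difference, so the stated 80% power belongs to a test that is not planned

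*Protocol article*

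**What the plan says.** Sample size calculation (Protocol article): "The trial was designed as a superiority trial with ODI as the primary observation index". The planning values come from a previous study. For the control arm the mean and "standard deviation of ODI after 4 weeks of intervention in the TCEs group were 19.73 and 1.94, respectively"; for the combined arm the corresponding values for "ODI after 4 weeks of intervention in the Tuina combined with TCE group were 14.53 and 2.60, respectively". The formula takes α = 0.05 (used as α/2), β = 0.2, σ = 2.60 and Δ = −4, and Δ is subtracted from μt − μc in the denominator. The result is "The sample size for each group was 74", and "the total number of cases was planned to be 166 cases, considering the potential for adverse effects". Allocation is 1:1 (Study design).

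Statistical analysis (Protocol article): "The purpose of the primary and secondary outcome indicators was to assess the difference in efficacy between the two groups". The between-group comparison over time uses a repeated-measures analysis of variance. On the threshold the section says "The level of statistical significance was set at 5" per cent, and 95% confidence intervals are to accompany the estimates. Neither this section nor any other mentions Δ, a margin, or a comparison of a confidence limit with −4.

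**The concern.** With Δ = −4 in the formula, the sample size section plans to reject H0: μt − μc ≥ −4, that is, to show that adding Tuina lowers ODI by more than 4 points. The analysis section plans to reject H0: μt − μc = 0. These are different hypotheses with different success criteria.

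Two things follow. The 80% power describes a test that nobody plans to run. And if superiority is declared when p < 0.05, it can be declared for an effect well short of the difference that the design was sized to exceed. An observed 3-point benefit, for example, would succeed under one section and fail under the other, and the document does not say which governs.

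**Working it through.** **Inputs**, all from Sample size calculation: μt = 14.53, μc = 19.73, so μt − μc = −5.20; σ = 2.60; Δ = −4; two-sided α = 0.05 (z = 1.960); power 80% (z = 0.842). Figures below use the normal approximation for a two-group comparison of 4-week means, the comparison that the protocol itself sized.

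**Step 1. Reproduce the 74.**

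- μt − μc − Δ = −5.20 + 4 = −1.20.
- Numerator: 2 × (1.960 + 0.842)² × 2.60² = 2 × 7.849 × 6.76 = 106.12.
- With the denominator squared: 106.12 / 1.44 = 73.7, rounded up to **74**. This matches.
- As printed, with no square on the denominator: 106.12 / (−1.20) = −88.4. The square is missing from the printed formula.
- With no margin (Δ = 0): 106.12 / 5.20² = 106.12 / 27.04 = 3.9, so **4** per group.
- Other readings also fail to give 74: a one-sided 5% level gives 59, SD 1.94 gives 42, and the root-mean-square SD of 2.29 gives 58.

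The margin alone moves the answer from 4 to 74, so it is a working part of the design.

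**Step 2. Where each test becomes significant.** The standard error of the difference is 2.60 × √(2/n).

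| | n = 74 per group | n = 83 per group (166 in total) |
|---|---|---|
| Standard error | 0.427 | 0.404 |
| Smallest observed benefit significant against zero (1.96 × SE) | 0.84 | 0.79 |
| Smallest observed benefit that passes the margin test (4 + 1.96 × SE) | 4.84 | 4.79 |

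On the ODI's 50-point scale, the first threshold is about one fifth of the 4-point margin (0.84 / 4 = 0.21).

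**Step 3. Probability of success with 74 per group.** Against zero this is Φ(δ/SE − 1.96); against the margin it is Φ((δ − 4)/SE − 1.96), where δ is the true benefit.

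| True benefit (points) | Test against zero | Margin test |
|---|---|---|
| 1.0 | 64.8% | practically 0 |
| 1.2 | 80.2% | practically 0 |
| 2.0 | 99.7% | practically 0 |
| 4.0 | > 99.9% | 2.5% |
| 5.2 | > 99.9% | 80.2% |

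With the noncentral t distribution the values hardly change: 64.2% at 1 point and 99.6% at 2 points against zero, and 79.6% for the margin test at 5.2 points. With 83 per group the margin test has 84.5% power at 5.2 points.

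**Step 4. Sensitivity to the SD.** If the true SD were larger (an assumption), the smallest benefit significant against zero with 74 per group would be 1.6 points at SD 5, 2.6 at SD 8 and 3.2 at SD 10. All remain below 4, so the gap between the two criteria does not depend on the small planning SD.

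**The case against.** The best counter-argument is that the article is condensed. It writes out no null hypothesis and no success rule, it already plans the 95% confidence interval that a margin comparison would need, and the exact rule may stand in a fuller document. Nor does it call Δ a margin or say anywhere that 4 points is a clinical threshold. A test against zero is amply powered on the stated inputs, and a reader given the estimate and its interval can see whether the effect exceeds 4.

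Part of this stands. The zero null is inferred from the stated aim, the method and the p-value threshold. The mismatch costs no power and does not inflate the type I error of a test against zero. The thresholds above are for a simple 4-week comparison, and those of a repeated-measures analysis over four time points would differ somewhat.

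It does not remove the contradiction. The article is not silent on the test: it names a method and a significance level, and these do not match the hypothesis from which its sample size was computed. A repeated-measures analysis of variance still has a null of no difference. The place of Δ in the formula, and the fact that 74 is reproduced only with it, leave no other reasonable reading.

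**Conclusion.** The concern holds. The 74 per group and the 80% power belong to a test of superiority by more than 4 ODI points, and the analysis section plans a test against zero. On the protocol's own inputs (SD 2.60, two-sided 5%, 4-week means, 74 per group), the two success criteria lie 4 points apart, at 0.84 and 4.84 observed points. The planned test has 80% power at a benefit of about 1.2 points and more than 99.9% at the assumed 5.2 points, so the quoted power does not describe it. The harm is in interpretation: a superiority claim could rest on about one fifth of the difference that the design set out to exceed. The exact thresholds rest on SD 2.60 and on a two-group comparison at 4 weeks; the mismatch itself does not.

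**What to change.** Choose one hypothesis, write it in both sections, and do so before results are seen.

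- **If the margin is meant:** state H0: μt − μc ≥ −4 and name the 4-week ODI difference (combined minus TCE) as the deciding comparison, since that is what was sized. Declare superiority only if the upper limit of its two-sided 95% confidence interval is below −4. Justify the 4 points. The figures 74 and 166 stay as they are provided SD 2.60 is realistic. With an assumed SD of 5, power for this test at 74 per group would be only about 31%.
- **If superiority over zero is meant:** delete Δ and restate what the sample delivers: with 74 per group and SD 2.60, about 80% power for a 1.2-point difference and above 99.9% for 5.2 points. Make clear that a significant result does not show a benefit of 4 points.

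In either case correct the printed formula. If Δ is kept, the denominator must be squared to give 74.

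The cost is a sentence or two in the sample size and analysis sections and no extra patients on the stated SD. The first option makes the success criterion stricter; the second means rewriting the stated power.

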In addition to these advantages, this study had some shortcomings. Firstly, due to the constraints of the intervention, blinding the treating physicians and the patients was not feasible. Consequently, any potential bias could only be mitigated by blinding the assessors. Secondly, the majority of the outcome indicators were subjective evaluators (e.g., ODI, SF-36, and SF-MPQ), which were vulnerable to patients’ subjective awareness, placebo effects and anticipated outcomes. Despite these limitations, these shortcomings will be addressed in future studies. This study will provide scientific evidence-based medical evidence for the efficacy and safety of Tuina combined with TCEs to improve dysfunction and pain in patients with LDH, and a more cost-effective, safe and effective treatment for LDH.

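### The 166 cases are said to allow a full evaluation of safety, but the number comes from the ODI alone, and zero serious events in 83 Tuina patients would exclude only true rates above about 4.3%

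*Protocol article*

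**What the plan says.** In the protocol article, the section Sample size calculation makes the ODI the primary index and derives the group size from it: "The sample size for each group was 74". It then moves to the planned total: "To evaluate the efficacy and safety of this study fully, the total number of cases was planned to be 166 cases". The reason added is "considering the potential for adverse effects". The section gives no adverse event rate, no risk to be detected or excluded, and no target for the width of a safety interval.

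The Introduction credits Tuina with a "low incidence of serious adverse effects", without a figure. The Abstract's conclusion expects the trial to supply an evidence base for safety as well as efficacy. The Discussion ends by promising evidence on both and "a more cost-effective, safe and effective treatment for LDH". The limitations listed there cover blinding and subjective outcomes; limited information on rare harms is not among them.

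**The concern.** The sample size section names full evaluation of safety as a purpose of the 166 cases, yet nothing in the calculation relates to safety. By the article's own account, serious harms of Tuina are uncommon. A single arm of this size says least about harms of that kind.

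At stake is how a clean result may be read. If few or no serious events occur, the sample size statement and the closing wording together invite the conclusion that adding lumbar manipulation to exercise is safe. A serious-event rate of a few per cent would still be compatible with the data. This holds even if events are defined and collected perfectly in both arms.

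**Working it through.** **Inputs from the protocol article.** Sample size calculation: total 166; two-sided alpha 0.05; beta 0.2; SD 2.60; margin -4; mean ODI (SD) "after 4 weeks of intervention in the TCEs group were 19.73 and 1.94, respectively" and "in the Tuina combined with TCE group were 14.53 and 2.60, respectively". Study design: patients "randomly assigned to either the TCE group or the Tuina combined with TCE group at a 1:1 ratio". Hence 166/2 = 83 per arm, which is derived and not stated. No event rate is given, so every rate used below is an assumption.

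**1. The plan's own figure.** Distance from the margin: |14.53 - 19.73 + 4| = 1.2.

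n = 2 × (1.96 + 0.84)² × 2.60² / 1.2² = 73.7 (unrounded normal quantiles), so 74 per group. The stated figure is reproduced. This needs the denominator squared; the formula as printed lacks the square and would give 88.4. That is a separate matter.

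**2. From 74 to 83.** 74 / (1 - 0.10) = 82.2, rounded up to 83 per arm, or 166 in total. The total equals a 10% allowance for losses. No safety quantity is needed to reach it.

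**3. What zero events would exclude.** Exact upper limits for 0 events in n patients are 1 - 0.025^(1/n) (two-sided 95%) and 1 - 0.05^(1/n) (one-sided 95%). They need no assumed rate.

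| Patients in the Tuina arm | Two-sided | One-sided |
|---|---|---|
| 83 | 4.35% | 3.54% |
| 74 (if only the calculated number is evaluable) | 4.86% | 3.97% |

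Pooling all 166 would give 2.2% and 1.8%, but only one arm receives Tuina, so the pooled limit does not answer the question about Tuina.

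**4. Chance of seeing no case among 83, (1 - p)^83.**

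| Assumed true rate p | No case seen | At least one case |
|---|---|---|
| 0.5% | 66% | 34% |
| 1% | 43% | 57% |
| 2% | 19% | 81% |
| 5% | 1.4% | 98.6% |

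The sample is thus informative for harms at about 5% and above, and weak at 1% and below. To exclude a 1% rate with zero events (one-sided 95%), log(0.05)/log(0.99) rounds up to 299 exposed patients.

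**5. Comparison between arms.** Fisher's exact test, 83 against 83, two-sided 0.05, by full enumeration, for assumed rates:

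- 1% against 5%: power 12%
- 5% against 10%: power 15%
- 5% against 15%: power 50%

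With no event in the control arm, 5 Tuina patients with an event give p = 0.059 and 6 give p = 0.028. Six of 83 is 7.2%.

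**The case against.** The strongest reply is that the sentence states a purpose. It claims no power, precision or detectable risk, and its mention of adverse effects most naturally means an allowance for patients lost. The arithmetic supports this, since 74/0.9 leads to 83. This stands, and it is why the fix asks the authors to say so if that is the intent.

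Safety is also wider than serious events. For commoner harms 83 patients are useful: an assumed 10% rate would be estimated to within about 6.5 points either way (1.96 × √(0.1 × 0.9/83)). This stands too, and it confines the point to uncommon serious harms.

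Efficacy trials are routinely sized on the primary outcome, and any arm of 83 has the same zero-event limit. That is true, but such trials do not usually present their size as sufficient for a full evaluation of safety.

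A reader might infer two stronger things that the article does not support. One is that the plan would declare the treatment safe on zero events. It sets no safety hypothesis, threshold or such rule, and the promise of safety is closing prose in the Discussion. Over-reading is a foreseeable risk and not a planned step. The other is that zero or one serious event per arm is the likely result. The article gives no rate. Moreover, the Adverse events section calls for termination of the trial on any serious adverse event. Read literally, that rule changes what a completed trial without serious events means.

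**Conclusion.** The point holds in a limited form. The sample size section attributes to the 166 cases a property that the design does not have for uncommon serious harms. The size follows from the ODI, with an increase that matches about 10% for losses. Zero serious events in the Tuina arm would leave true rates up to about 4.3% (two-sided) or 3.5% (one-sided) compatible with the data, so the unqualified safety wording in the Discussion claims more than can be shown.

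The limits rest on 83 patients per arm, derived from 166 and 1:1 allocation, and on all of them being evaluable; with 74 they are 4.9% and 4.0%. The detection probabilities and powers rest on assumed rates and are illustrations only. Severity is minor: the defect lies in wording and interpretation, and neither the primary analysis nor the number of patients needs to change.

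**What to change.** 1. In Sample size calculation, drop the statement that 166 cases evaluate safety fully. Say that the ODI sets the size, that the increase from 148 to 166 is an allowance for losses (if that is the intent), and that safety is descriptive. Give the achieved precision: with no event among 83 patients, only true rates above about 4.3% are excluded (two-sided 95%).
2. Report, for each arm, the patients with at least one adverse event, with exact 95% confidence intervals.
3. In the Abstract's conclusion and the Discussion, limit the safety conclusion to that bound, and add limited information on rare harms to the limitations.
4. Reconcile the Adverse events section with this summary. Its monitoring sentence names only patients who received Tuina with the exercises, whereas a summary by arm needs both groups. Its termination wording leaves open whether one patient's participation or the whole trial is meant, and the authors must settle this so that readers know what a completed trial without serious events shows.

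The cost is a few sentences and one table, with no extra patients. The downside is a less favourable safety claim.
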